
### Data analysis and hypothesis testing

#### Study 1: prospective longitudinal study

Missing values analysis will be performed for each variable. If the results support the assumption of values missing at random or completely at random, they will be imputed via multiple imputation. Within the framework of sensitivity analysis, the hypotheses will be tested with both the raw dataset and the imputed dataset.

##### Hypothesis 1

To test hypothesis H1, the PD outcome variable dataset collected in study 1 will be matched to the CD outcome variable dataset using participants’ national health insurance numbers, which are pseudonymized by a data trustee in accordance with German data protection laws. Three dimensions of diagnostic validation will be evaluated to assess whether the CD variables can serve as proxies for the PD variables (see section “Study outcomes”): accuracy, reproducibility, and precision [46].

Accuracy will be assessed by linear regression, with each PD outcome variable as a dependent and each CD outcome variable as an independent variable. 95% confidence intervals (CIs) will be calculated for the identified intercepts and regression coefficients using the Gaussian approach (95%-CI of a: a ± 2*Se_a_; 95%-CI of b: b ± 2*SE_b_). If the CIs include 0 and 1 (for intercepts and regression coefficients, respectively), accuracy will be considered adequate for the outcome variable.

Reproducibility will be assessed by duplicate standard deviation (SD), which is calculated using the following formula (with *d* as the individual difference between the CD outcome variable and approximated PD outcome variable for each patient):$$\varvec{D}\varvec{u}\varvec{p}\varvec{l}\varvec{i}\varvec{c}\varvec{a}\varvec{t}\varvec{e} \varvec{S}\varvec{D}=\sqrt{1/2\left(\frac{\sum {\varvec{d}}^{2}}{\varvec{n}}\right)}$$

Following the recommendation by Cleophas & Zwinderman [46], reproducibility is considered adequate for a duplicate SD of 10–20%.

Precision will be assessed by comparing the standard deviations of CD outcome variable and approximated PD outcome variable. If the standard deviation of a CD outcome variable is equal or smaller to the standard deviation of an approximated PD outcome variable, precision is considered good or better.

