If at least two of the three validation criteria are met, the tested CD outcome variable is considered an adequate proxy for the respective PD outcome variable. Bland-Altman plots will be used for graphic evaluation of measurement differences [47, 48]. This same procedure will be applied to test H1b using CD quality indicators and PD quality indicators, which are represented by facility group mean values of PD outcome variables.

##### Hypothesis 2

H2 postulates an improvement in risk-adjustment models when considering cross-sectoral claims data, i.e., an increase in (adjusted) R^2^, and will be analyzed with nested multilevel regression models. A basic model (M0) will be estimated for each PD outcome variable using the PD confounders (see Table 2) on level 1. Models will be estimated for each time point after baseline (t1, t2, t3), and will be adjusted for *time* (rehabilitation effect) as a predictor on level 2. Furthermore, level 2 PD quality indicators will be included. Each model will be expanded with previously identified CD risk factors (on level 1 and level 2) as described in section “Study outcomes”. The nested models will be compared with Likelihood Ratio tests [49]. The analysis sample will be randomly divided into two parts, with one half allocated for analysis of risk-adjustment, and the remaining half used to validate the resulting models.

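### The precision criterion compares between-patient spread, so at patient level meeting accuracy practically guarantees it, and near-uninformative claims variables can pass the two-of-three rule

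*Protocol article*

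**What the plan says.** The rule stands in the Protocol article under Data analysis and hypothesis testing, Study 1, Hypothesis 1.

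- **Accuracy:** "Accuracy will be assessed by linear regression, with each PD outcome variable as a dependent and each CD outcome variable as an independent variable". The intervals are the estimate ± 2 SE. The criterion is: "If the CIs include 0 and 1 (for intercepts and regression coefficients, respectively), accuracy will be considered adequate for the outcome variable".
- **Reproducibility:** based on the duplicate SD of the CD–PD differences; "reproducibility is considered adequate for a duplicate SD of 10–20" per cent. The base of the percentage is not given.
- **Precision:** met under this condition: "If the standard deviation of a CD outcome variable is equal or smaller to the standard deviation of an approximated PD outcome variable". No repeated measurement is described, so each SD is taken across patients.
- **Decision:** "If at least two of the three validation criteria are met, the tested CD outcome variable is considered an adequate proxy".
- **Facility level:** "This same procedure will be applied to test H1b using CD quality indicators and PD quality indicators", the latter being facility means.

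No minimum correlation or R² is among the three criteria. Under Hypotheses, H1a nevertheless claims a high patient-level association between CD and PD outcomes.

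**The concern.** An SD across patients mixes true differences between patients with error. A smaller SD does not show a more precise measure, and a constant would score best. The comparison also depends on units: a 0/1 claims variable, such as receipt of a mobility aid, has an SD of at most 0.5 and wins against any score with a larger SD, whatever it measures. At facility level the criterion rewards indicators that hardly distinguish one facility from another, which is the opposite of what a quality indicator is for.

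The second problem is how precision interacts with accuracy. Accuracy regresses PD on CD and asks for slope 1, and that alone nearly fixes the order of the two SDs. Precision then adds a second vote without adding evidence. This rule decides whether claims data may replace patient- and physician-reported data, so its errors run towards false acceptance.

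**Working it through.** **Inputs from the article.** 600 patients; 20% dropout at each of three post-baseline time points; about 300 left for analysis; matched data split in two (about 150 each if halved); ten facilities; CI = estimate ± 2 SE.

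**The article's own figure.** 600 × 0.8³ = 307, against the stated 300. This agrees, so n = 300 and n = 150 are used for H1a and n = 10 for H1b.

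**Assumptions.** The article gives no PD means or SDs. I used bivariate normal data with mean 50 and SD 20 (CV 40%), and SD 12.5 (CV 25%) where stated. Reproducibility was scored as met if the duplicate SD was at most 20% of the mean, counting values below 10% as adequate. The PD quantity in the precision criterion is read as the observed PD variable.

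**Step 1: algebra.** Let k = SD(CD)/SD(PD).

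- Slope: b = r/k.
- Standard error: SE(b) = (1/k) × √((1 − r²)/(n − 2)).
- At b = 1, k = r ≤ 1, so precision is met.

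Meeting accuracy while failing precision needs k > 1 and b + 2 SE(b) ≥ 1, that is, 1 < k ≤ r + 2√((1 − r²)/(n − 2)). This is possible only if (1 − r)/(1 + r) < 4/(n − 2). The largest k that any r allows is √(1 + 4/(n − 2)).

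| n | 4/(n − 2) | Sample r needed | Largest SD(CD)/SD(PD) |
|---|---|---|---|
| 300 | 0.0134 | 0.9735 | 1.007 |
| 150 | 0.0270 | 0.947 | 1.013 |
| 10 | 0.5 | 0.333 | 1.225 |

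**Step 2: patient level, simulated.** For calibrated variables (true slope 1, intercept 0) with r from 0.1 to 0.9, precision given accuracy was 100% at both n = 300 and n = 150 (4,000 runs each). At n = 300:

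- r = 0.1 (R² = 1%): declared adequate in 94.6% of runs; reproducibility met in 0%. The duplicate SD is 20 × √(0.99/2) = 14.1, or 28% of the mean.
- r = 0.3: declared adequate in about 95%; reproducibility met in 0%.
- r = 0.1 with assumed mean 30 and SD 18: declared adequate in about 95%; duplicate SD 18 × √(0.99/2)/30 = 42%.

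**Step 3: the route without accuracy.** Take r = 0, equal means, k = 0.5, PD CV 25%, n = 300.

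- Accuracy: b is near 0 with SE = 2 × √(1/298) = 0.116, so the CI does not reach 1. Accuracy failed in every run.
- Precision: always met.
- Duplicate SD: 12.5 × √(1.25/2) = 9.88, or 19.8% of 50, just inside 20%.
- Result: accepted in 61–63% of runs across repeated simulations.

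This route depends on the PD CV. With CV 40% the duplicate SD is about 32% and acceptance is 0%. In the limit, a constant at the PD mean has duplicate SD = SD(PD)/√2 and meets both criteria whenever the PD CV is at most 0.2 × √2 = 28.3%.

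**Step 4: ten facilities (20,000 runs).** Precision given accuracy:

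| r | Equal SDs | True slope 1 |
|---|---|---|
| 0.7 | 69–70% | 95% |
| 0.9 | 58% | 78% |

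The CI is wide enough here that accuracy no longer settles precision.

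**The case against.** **The rule does not reduce to accuracy alone.** A reader might infer that it does, and that is wrong. The rule is accuracy, or else precision together with reproducibility. Step 3 shows variables accepted without accuracy. What stands is that accuracy is sufficient at patient level, not that it is necessary.

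**It does not cover every claims variable at both levels.** A reader might extend the result to H1b. With ten facilities the sample correlation needed for a conflict falls to 0.33, and precision follows accuracy in only 58–70% of cases with equal SDs at r = 0.7 to 0.9. Near-certainty there needs a true slope of 1 and a modest correlation.

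**The article never calls the criteria independent.** Correct. It names three dimensions and a two-of-three count, and no broken promise of independence should be attributed to it.

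**The r = 0.1 example is constructed, and accuracy shares the blame.** Partly fair. No CD outcome is fixed yet, and such a variable would need the PD mean and a tenth of the PD SD. The accuracy criterion also has no minimum r and no limit on CI width. But the two-of-three count would have stopped this variable had the second vote carried information.

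**Other safeguards exist.** Bland-Altman plots are planned and a correlation above 0.30 is expected for H1b. The plots are for graphic evaluation and the correlation is an assumption for H1b; neither is a vote in the rule.

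**The PD quantity could mean the regression-fitted value.** Precision would then require |b| ≥ 1, which a calibrated variable meets about half the time. That is the less natural reading, and it would only restate the slope, so it would not measure precision either.

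**Conclusion.** The point holds in limited form. The precision criterion measures between-subject spread. At patient level (n about 150 to 300), practically every variable that meets accuracy also meets precision; exceptions need a sample r of at least 0.947 to 0.9735, where the duplicate SD is small anyway. Accuracy alone therefore suffices, and a calibrated variable sharing 1% of variance with PD is accepted in about 95% of samples, which conflicts with the high association claimed in H1a. A second route can accept an unrelated variable, but its size depends on the PD CV. At facility level the redundancy is not automatic, though the criterion still points the wrong way.

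The thresholds are algebraic and need only n and the ± 2 SE rule. The reproducibility results rest on assumed PD means and SDs, on the mean as the base of the percentage, and on reading the PD quantity as the observed variable.

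**What to change.** - Remove the SD comparison from the vote, and require both accuracy and reproducibility or agreement.
- If a precision measure is kept, use the residual SD of PD given CD, SD(PD) × √(1 − r²), against a limit fixed before the data are linked.
- State that the PD quantity in the criterion is the observed PD variable.
- Do not replace the criterion at facility level with a preference for a large raw between-facility SD. With about 300/10 = 30 analysed patients per facility, that SD also contains sampling error.

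This changes the wording of the decision rule only and needs no new data. The cost is that fewer claims variables will be declared adequate.

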#### Hypotheses

Using a sample of primary knee or hip replacement patients in orthopedic follow-up rehabilitation, we will test the following hypotheses:

H1a: Patient-level outcomes (outcome variables) based on claims data (CD outcome variables) show high association with patient-level outcomes as measured by a primary data quality assurance protocol currently considered best practice (PD outcome variables).

H1b: Similarly, facility-level outcomes (quality indicators) based on cross-sectoral SHI claims data (CD quality indicators) are correlated with facility-level outcomes based on the current best-practice quality assurance protocol collecting primary data (PD quality indicators).

H2: A risk-adjustment model for rehabilitation outcomes as measured by PD outcome variables improves when utilizing risk factors based on cross-sectoral SHI claims data (risk factors on patient- and facility levels) compared to a risk-adjustment model without CD risk factors.

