#### Study 2: retrospective cohort study

Since study 2 is exploratory in nature, no CD outcomes have yet been identified. The following steps will be taken for selection and operationalization of CD outcome variables, CD quality indicators, and CD risk factors:

A structured search for existing quality indicators, outcome variables, and risk factors of orthopedic rehabilitation will be conducted in (a) literature (e.g., Medline, Cochrane Library), (b) medical guidelines (Guidelines International Network), (c) indicator databases (e.g., [42, 43], and (d) documentation of existing procedures of quality assurance in the field of orthopedic rehabilitation. Search results will be assessed for their compatibility with claims data.The nationwide project claims database of AOK-insured patients will be analyzed to identify additional complex healthcare and rehabilitation outcomes for patients that have undergone primary knee or hip arthroplasty. This includes analysis of demographics, medical and other relevant data such as comorbidities, nursing care level, medication use, and utilization of therapeutic health service. The database will encompass data from the individual observational period for each patient, which includes the 24 months pre-surgery as well as 12 months of care after orthopedic rehabilitation. Pre-surgery data will be used as a baseline measure of study population characteristics, while the follow-up period after rehabilitation can be used to identify individual changes in relation to the baseline.Results from step (1) and (2) will be consolidated and CD outcomes and risk factors operationalized. Potential CD outcomes that represent aspects of rehabilitation treatment quality within claims data could be, for example, mobility (through provision of mobility aids), pain medication, or progression to higher nursing care levels. CD outcomes will consider care and quality aspects from all medical sectors. All quality indicators will be defined by denominators and numerators, and descriptions of inclusion, exclusion and exception criteria [44]. Denominators display a specified target population (e.g., all patients undergoing arthroplasty), whereas numerators display the number of people in the target population experiencing a specified outcome (e.g., surgical complications; [44]). These descriptive definitions can later be used to calculate individual values for rehabilitation facilities. Indicators will be translated into coded data (e.g., coded diagnoses, procedures, and prescriptions), and an appropriate reference value will be defined for each indicator.Each CD quality indicator will be adjusted for risk factors that have statistical influence on the indicator rate but cannot be influenced by IRFs. Risk factors might include patient characteristics (e.g., age, sex, comorbidity, nursing care level), or aspects of acute hospital care before rehabilitation. Relevant risk factors will be selected based on current research, results from SHI data analyses, and expert opinion [45].

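### The two-of-three proxy rule for H1 depends on measurement units and requires no strength of association, so it does not test H1a or H1b

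*Protocol article*

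**What the plan says.** The rule is in the protocol article under Data analysis and hypothesis testing, Study 1, Hypothesis 1.

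- **Accuracy.** A linear regression is fitted "with each PD outcome variable as a dependent and each CD outcome variable as an independent variable". The pass condition is: "If the CIs include 0 and 1 (for intercepts and regression coefficients, respectively), accuracy will be considered adequate for the outcome variable". Intervals are the estimate ± 2 SE.
- **Reproducibility.** The duplicate SD is the square root of half the mean of d², with d defined "as the individual difference between the CD outcome variable and approximated PD outcome variable for each patient". The cut-off is: "reproducibility is considered adequate for a duplicate SD of 10–20" per cent. The article does not say per cent of what.
- **Precision.** The condition is: "If the standard deviation of a CD outcome variable is equal or smaller to the standard deviation of an approximated PD outcome variable", in which case precision counts as good or better.
- **Decision.** "If at least two of the three validation criteria are met, the tested CD outcome variable is considered an adequate proxy". No single criterion is mandatory. Bland-Altman plots are for graphic evaluation only. The same procedure is applied to H1b, with facility means as PD quality indicators.

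Under Hypotheses, H1a states that CD outcomes "show high association with patient-level outcomes as measured by a primary data quality assurance protocol". Under Study design and methods, H1b is tied to a correlation above 0.30, which the article calls moderate. Under Study outcomes, Study 2, possible CD outcomes are "mobility (through provision of mobility aids), pain medication, or progression to higher nursing care levels". Table 2 lists the PD outcomes: SMFA-D, a pain visual analogue scale, FESS, the 6-minute walk test, the Harris Hip Score and the Knee Society Score.

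**The concern.** An intercept of 0, a slope of 1, a difference CD − PD and a comparison of SDs are tools for two methods that measure the same quantity in the same unit. A prescription flag and a pain score are not such a pair, and the article describes no conversion to a common scale. A verdict can therefore change when a variable is merely relabelled.

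The rule also does not ask what the hypotheses assert. The slope is a measure of association, but it is checked only for compatibility with 1. That check passes more easily when the standard error is large, and the other two criteria together can bypass it. The spread between patients is not measurement precision either: a CD variable with almost no variation satisfies the third criterion.

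This rule decides which claims variables may replace questionnaires. The Discussion adds that failure to find suitable claims indicators would show the questionnaire protocol to be still best practice. Rejections caused by units would lead to that conclusion whatever the true association.

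**Working it through.** **Inputs from the article.** Ten facilities; 600 recruited; 20% dropout per time point; about 300 left for analysis. Check: 600 × 0.8³ = 307, which agrees with 300. The article states no error rate or power for the rule.

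**Assumptions.** The article gives no means or SDs, so those below (written mean/SD) are illustrative. Duplicate SD is taken as a percentage of the PD mean and passes at 20% or less. The approximated PD variable is read in two ways: as observed PD, or as the value fitted by the regression. Simulations used 3,000 to 4,000 runs per scenario.

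**1. Yes/no CD, strong association (n = 300).** Half the patients have CD = 0 with mean pain 20, half have CD = 1 with mean pain 50; residual SD 5.

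- SD(PD) = √(15² + 5²) = 15.8, so r = 15/15.8 = 0.95.
- Accuracy: slope 30, SE = 5/√(300 × 0.25) = 0.58, CI about 28.8 to 31.2. Intercept 20, SE = 5/√150 = 0.41, CI about 19.2 to 20.8. Fails.
- Reproducibility: mean d² = (20² + 49²)/2 + 5² = 1425.5; duplicate SD = √712.75 = 26.7, or 76% of the PD mean of 35. Fails. With fitted values, √(1400.5/2) = 26.5, or 76%. Fails.
- Precision: SD(CD) = 0.5, below 15.8 (observed) and 15 (fitted). Passes.

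One of three is met. Simulated acceptance is 0% on both readings. A yes/no CD unrelated to a 30/20 pain score is also accepted in 0%, so the rule does not separate the two.

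**2. The same facility indicator in two units (10 facilities, r = 0.9, PD 30/4).**

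| | CD as percentage (30/3.5) | CD as proportion (0.30/0.035) |
|---|---|---|
| Slope = r × SD(PD)/SD(CD) | 1.03 | 103 |
| SE of slope = 4√(1 − 0.81)/(SD(CD) × √9) | 0.17 | 16.6 |
| Slope CI (± 2 SE) | 0.70 to 1.36 | 70 to 136 |
| Mean d² | 16 + 12.25 − 25.2 = 3.05 | 29.7² + 15.75 = 897.8 |
| Duplicate SD / 30 | 4% | 71% |
| Simulated acceptance | 97% | about 1% |

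The acceptance figures hold on both readings. The data are identical; only the label changes.

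**3. Unrelated CD (r = 0, n = 300).** With equal means m, the expected duplicate SD on the observed-PD reading is √((SD(PD)² + SD(CD)²)/2)/m.

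| PD | CD | Duplicate SD / m | Accepted, observed PD | Accepted, fitted PD |
|---|---|---|---|---|
| 50/10 | 50/1 | √50.5/50 = 14% | 100% | 65% |
| 50/10 | 50/8 | √82/50 = 18% | 99% | 0% |
| 40/10 | 40/8 | √82/40 = 23% | under 1% | 0% |
| 30/20 | 30/18 | √362/30 = 63% | 0% | 0% |

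In the first row the slope SE is 10/(1 × √300) = 0.58. The interval around a true slope of 0 is then about ± 1.15 and often reaches 1, so imprecision helps accuracy to pass.

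**4. What H1b can show at ten facilities.** A Fisher-z 95% CI around r = 0.30 is −0.41 to 0.78 for n = 10, against 0.19 to 0.40 for n = 300.

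**The case against.** The strongest reply has four parts.

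- **The rule does contain a measure of association.** A reader might infer that it contains none. That is too strong: the regression slope is one. What stands is that no strength is required and that the slope can be bypassed.
- **Acceptance of unrelated variables is conditional.** A reader might take the 99% in the second row of the last table as typical. It is not: it sits just inside the 20% limit, falls below 1% when both means are 40, and is 0% on the fitted-value reading. Likewise, a same-unit variable with r = 0.8, means of 50 and both SDs at 20 is accepted in 49% of runs on the observed-PD reading, but in 92% once the CD SD is 19. These figures show sensitivity to scale, not general error rates.
- **CD might first be rescaled through the regression.** Fitted values would then meet accuracy and precision against observed PD at any r. But the article describes no such step; it compares CD itself with approximated PD, so this cannot be held against the plan as written.
- **CD outcomes are not yet chosen, and the base of the 10–20% may be in the cited textbook.** Both are fair. The examples are only possibilities, and the missing base alone would be a detail of condensation. The unit dependence remains, because the article fixes the criteria and the decision rule itself.

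**Conclusion.** The point holds as a defect in the stated rule, not as missing detail. The criteria presuppose a common unit that the article's own examples lack, and none sets the strength of association that H1a and H1b assert. The hypotheses and the decision rule need to be reconciled.

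The firm results do not depend on how approximated PD is read: a yes/no CD with r = 0.95 is accepted in 0% of runs, and one facility indicator with r = 0.9 goes from 97% to about 1% when a percentage is written as a proportion. They rest on assumed scale values and on duplicate SD as a percentage of the PD mean.

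Acceptance of unrelated CD is possible but not general. It needs CD close to the PD scale and mean, and at n = 300 ranges from 0% to 100% with the means and SDs. The documents do not support the broader inference that the rule usually accepts unrelated claims variables.

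**What to change.** Replace the two-of-three rule by a unit-free association criterion as the necessary condition.

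- **H1a.** For each CD–PD pair, report a correlation or R² for continuous CD, and an AUC or standardised mean difference for binary CD. Give a 95% CI that allows for clustering, with a small-sample correction because there are only ten facilities. Fix a numeric threshold for high association before the CD and PD data are linked. The article gives no value, so the investigators must set it; since they call a correlation above 0.30 moderate, on the correlation scale it should lie above that.
- **H1b.** Use the correlation above 0.30 already stated under Study design and methods, and report it with its CI. State that this CI will be wide at ten facilities.
- **Calibration and Bland-Altman plots.** Keep them only for cross-validated predictions of PD expressed on the PD scale.
- **SD comparison.** Drop it as a pass criterion.

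The cost is a rewording of the Hypothesis 1 analysis; no extra data are needed. The downside is that fewer CD variables may be declared adequate.

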**Fig. 1 Fig1:**
[figure not shown]
Data flow in SEQUAR

We will use the matched dataset to test our hypotheses:

For H1a, CD outcome variables should be able to serve as surrogates (proxies) for rehabilitation treatment outcomes as measured by current best-practice assessment (PD outcome variables; see outcome assessment and study design in high-quality studies on the effectiveness of multidisciplinary orthopedic rehabilitation—e.g., [28]). For H1b, we assume at least a moderate correlation (> 0.30) between CD quality indicators and PD quality indicators. To test H2, the impact of cross-sectoral CD risk factors (on patient and facility levels) on current risk-adjustment models for quality assessment will be investigated.

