### Study population and recruitment

#### Study 1: prospective longitudinal study

For study 1, ten German inpatient rehabilitation facilities (IRFs) were enlisted in the study by local representatives of the regional AOK health insurance funds, which in turn are recruiting a planned sample of 600 patients. Participating IRFs signed a collaboration agreement with the principal investigator, and each appointed a local study coordinator in charge of organization and implementation of all project tasks (e.g., recruitment of participants, distribution of patient information and consent forms, storing/safekeeping signed consent forms). Patient recruitment began in November of 2022 and will end in December 2023.

Patients eligible for participation are recruited on-site in the beginning of their orthopedic follow-up rehabilitation. Study coordinators present them with a physical copy of the study fact sheet (covering study synopsis, data protection, and other legal aspects), and ask for their participation. Those agreeing to participate sign an informed consent form. Eligibility is determined by meeting the inclusion criteria: Participants must be at least 18 years old at time of inclusion (beginning of rehabilitation), insured through AOK health insurance fund (for purposes of data availability), and receive inpatient orthopedic follow-up rehabilitation after implantation of a knee joint replacement or hip joint replacement due to osteoarthritis. Participants need to demonstrate sufficient knowledge of the German language and sufficient cognitive abilities to answer the comprehensive questionnaires independently. Patients that prematurely discontinue rehabilitation, demonstrate insufficient German or cognitive skills, or change health insurance within the study period will be excluded.

Participation in the study is incentivized with a €50 gift voucher for patients that complete all four questionnaires, while IRFs receive €120 per patient for full patient participation and completed case report forms.

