## Discussion

Health claims data has the potential to simplify current quality assessments in rehabilitation. SEQUAR will evaluate its benefit to quality assurance in orthopedic inpatient rehabilitation: We will explore outcome variables and quality indicators based on readily available statutory health insurance (SHI) claims data, and assess their ability to replace select parts of the current best-practice quality assurance protocol based on arduous primary data collection. If we fail to identify suitable claims data quality indicators, we can demonstrate that the current protocol of assessing patient-reported and physician-reported outcomes via questionnaires is still to be considered the best-practice approach. In the process, we are hoping to improve risk-adjustment models used to evaluate inpatient rehabilitation facility (IRF) quality by incorporating cross-sectoral SHI quality data (i.e., quality of the operating hospital) that could help adjust for risks outside of an IRF’s control.

Many previous studies have explored the utility of claims data in quality of care research. Some have even taken a cross-sectoral approach, like Stegbauer et al. [51] or Bramesfeld et al. [52], though the latter had to cut their trial phase short because–fittingly–the burden of primary data collection for participating physicians proved to be too great. However, to our knowledge, no study has examined claims data’s cross-sectoral potential for quality assurance in inpatient rehabilitation (where quality assessment is particularly difficult due to the variety in outcomes), nor has any research explored the possibility of replacing patient- and physician-reported outcomes with outcomes based on claims data.

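### H1b is stated as a facility-level correlation above 0.30, but the procedure assigned to it computes no correlation, and only ten facilities supply the primary-data indicators

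*Protocol article*

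**What the plan says.** - **Hypothesis.** Under Hypotheses, H1b says that facility-level CD indicators "are correlated with facility-level outcomes based on the current best-practice quality assurance protocol". Study design and methods adds the size: "we assume at least a moderate correlation (> 0.30) between CD quality indicators and PD quality indicators".
- **Test.** Under Data analysis and hypothesis testing, Hypothesis 1, the article describes the H1a procedure and then says: "This same procedure will be applied to test H1b using CD quality indicators and PD quality indicators". That procedure has three criteria:
  - accuracy: the interval for the regression intercept includes 0 and the interval for the slope includes 1;
  - reproducibility: a duplicate SD of 10–20%;
  - precision: the SD of the CD variable is no larger than that of the PD variable.

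  The decision rule is "If at least two of the three validation criteria are met". Bland-Altman plots are added for graphical inspection.
- **Unit of analysis.** PD quality indicators are facility means, and "ten German inpatient rehabilitation facilities (IRFs) were enlisted in the study".
- **Negative result.** The Discussion says that if no suitable CD indicators are identified, "we can demonstrate that the current protocol of assessing patient-reported and physician-reported outcomes via questionnaires is still to be considered the best-practice approach".

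**The concern.** The hypothesis and its test concern different things. A correlation measures how closely two indicators rank and track facilities, whatever their units. The assigned rule asks whether the two are numerically interchangeable, and two of its three criteria (duplicate SD and SD comparison) can be met with no association at all. The mismatch is sharper because Study outcomes defines CD indicators as numerator/denominator rates while PD indicators are scale means. An intercept of 0 and a slope of 1 have no natural meaning between those two without a rescaling that the article does not describe.

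The stake is practical. The end products are a quality assurance protocol that relies partly on claims data and report cards for the facilities. An indicator could be accepted for reasons unrelated to whether it tracks the questionnaire result, or rejected although it does. The Discussion also attaches a firm conclusion to a negative result that ten facility points cannot carry.

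**Working it through.** **1. The plan's own figures.** The sample-size section gives a patient flow only: 600/0.70 = 857 (stated 860) and 600 × 0.8³ = 307 (stated 300). Both reproduce. No precision or power figure is given for H1b, so there is none to check.

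**2. Number of points.** There is one PD mean per facility and ten facilities, so n = 10. The nationwide claims file (about 312,000 patients) adds none, because PD indicators exist only for the enrolled facilities. More patients or time points add no independent facilities either.

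**3. What the slope criterion demands.** In a regression of PD on CD, slope = r × SD(PD)/SD(CD). A slope of 1 therefore requires r = SD(CD)/SD(PD):
- equal SDs: r = 1;
- CD SD half of PD SD: r = 0.5;
- CD SD 1.5 times PD SD: r = 1.5, which is impossible. At r = 0.8 the slope is 0.8/1.5 = 0.53.

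The criterion is tied to relative spread, and 0.30 plays no part in it.

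**4. How the two-of-three rule behaves on ten points.** I simulated bivariate normal facility values and applied the rule as written (estimate ± 2 SE). Assumptions not in the article: PD mean 50, PD SD 5, duplicate SD expressed as a percentage of the PD mean, and 20% or less counted as adequate.

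| CD mean | SD(CD)/SD(PD) | True correlation | Rule passed |
|---|---|---|---|
| 50 | 1.0 | 0 | 52% |
| 50 | 0.5 | 0 | 98% |
| 30 | 1.0 | 0 | 3% |
| 30 | 0.5 | 0 | 35% |
| 50 | 1.0 | 0.5 | 63% |
| 50 | 0.5 | 0.5 | 99% |
| 50 | 1.5 | 0.8 | 14% |

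If 10–20% is read as a strict band, the first two rows become about 38% and 71%. At a common mean and equal SDs, moving the true correlation from 0 to 0.5 raises the pass rate by only 11 points (52% to 63%). Changing spread or scale moves it far more.

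**5. What ten facilities could say about a correlation of 0.30.** Fisher z: atanh(0.30) = 0.310; half-width 1.96/√(10 − 3) = 0.741. The limits are tanh(0.310 − 0.741) = -0.41 and tanh(0.310 + 0.741) = 0.78.
- The lower limit exceeds 0.30 only if the observed r is above 0.78.
- The upper limit is below 0.30 only if the observed r is under -0.41.
- Significance against zero (two-sided 0.05, 8 df) needs r = 2.306/√(8 + 2.306²) = 0.63.
- By simulation, the observed r exceeds 0.30 in 20% of samples when the true correlation is 0.

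**The case against.** Several objections have force.

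- **The SAP may add a correlation.** This does not dispose of the point. The article does not leave the H1b test open; it names a different procedure for it.
- **The word assume may state an expected size, not a test threshold.** That is possible. The hypothesis itself still says the indicators are correlated, and nothing in the analysis estimates a correlation.
- **The pass rates rest on an invented scale.** This is right. With a CD mean of 30 in place of 50, the rate for an unrelated indicator falls from 52–98% to 3–35%. No single rate should be quoted as the error rate of the rule. That the result moves so far with scaling is itself the finding.
- **A reader might infer that good indicators will probably fail.** The documents do not support this. Low power for a correlation concerns a test that is not planned; under the planned rule, with a common mean, an indicator with true correlation 0.5 passes in 63% to 99% of runs.
- **A reader might infer that H1b can never be supported with ten facilities.** This too goes too far. If a correlation were reported, an observed r above about 0.78 would put the whole interval above 0.30.
- **The intervals are labelled 95% but use ± 2 SE.** With 8 df the coverage is 91.9% (the multiplier would be 2.306). The label is inexact, but t quantiles would not repair the criterion. Wider intervals include 0 and 1 more easily: for an unrelated indicator with equal SDs, accuracy passes rise from about 22% to 30%.

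**Conclusion.** The point holds: followed as written, the plan does not test H1b as stated. The contradiction between the hypothesis and its assigned procedure needs no assumption. Nor does the count of ten facilities.

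The simulated pass rates do rest on assumptions (normality, chosen means and SDs, the reading of the 10–20% criterion). They show only that acceptance is governed by spread and scaling more than by association. The interval of -0.41 to 0.78 around an observed 0.30 rests on the usual Fisher approximation. It shows that an observed correlation of the moderate size the article names could be neither confirmed as above 0.30 nor excluded. The Discussion's statement about a negative result is unsupported for that reason, and not because failure has been shown to be likely.

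**What to change.** 1. Under Hypothesis 1, make the facility-level correlation between CD and PD indicators, with its 95% CI read against 0.30, the analysis for H1b. The three criteria and the Bland-Altman plots may stay as description, but the two-of-three rule should not decide H1b.
2. Label H1b as exploratory estimation on ten facilities.
3. In the Discussion, replace the claim to demonstrate with wording that failure to identify indicators would be inconclusive unless the CI excludes a correlation of 0.30.

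**Cost.** Wording only; no further facilities or data. The H1b claim becomes more modest, and most results will be inconclusive. By simulation, at a true correlation of 0 the interval lies wholly below 0.30 in about 12% of samples. At a true 0.5 it lies wholly above 0.30 in about 10%.
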